## Criteria for discontinuing intervention

All participants have the option to withdraw from the study and ask their samples and/or data to be destroyed at any time without the need to give a reason. However, whenever possible, reasons for dropping out will be recorded. In case adverse effects are identified, they will be explored and may result in the intervention being discontinued for the participants.

### Adherence and feasibility

A previous study has shown a dropout rate of 5% [51]. However, the dropout rate may be higher in the MEDITAGING project since 25.2% of the Portuguese immigrants plan to commute between Portugal and Luxembourg [66]. The adherence of home practice in a previous review has shown to be around 60% [67]. To increase adherence, weekly feedback will be requested from participants throughout the intervention, in order to detect and resolve any situation that needs attention.

Due to the under-researched target population of the MEDITAGING study, it has a secondary aim of investigating the operational feasibility of the MBSR for older migrants, as well as the financial, physical, and psychological feasibility of participating in the program. In particular, the following aspects will be evaluated: if participants both, those remaining in the study and those lost to follow-up, report [1] the need of any adjustment in the program [2]; any difficulties encountered (e.g., time restriction, physical limitation, anxiety, financial problems).

For the adherence and dropout rate analysis, the proportion of participants who completed the baseline assessment and went to the first group session and the number of participants that attended at least three sessions will be considered.

### Outcome measures

As outcome variables, we will assess executive functioning as primary outcome, as well as general cognitive ability, sleep quality, perceived stress, depression, anxiety, mindfulness-trait, cortisol level, and heart rate variability (HRV) as secondary ones. Additional exploratory analyses will be done to verify if the effects are moderated by demographic factors, such as gender and educational level, as well as number of attended sessions, stress, depression, mindfulness trait, anxiety, cortisol level, and sleep quality. We anticipate that the MBSR group will present gains (post-intervention compared to baseline) in cognitive tasks and stress relief and these gains will be higher than in the control group (health promotion program). A summary of the outcome measures is provided in Table 4. We aimed to select brief measures to minimize participant fatigue.

**Table 4 Tab4:** Summary of primary and secondary outcomes

Outcome	Construct/surrogate	Description
***Primary outcomes***		
TMT (Cavaco et al., 2013)	Executive functions	TMT Part A evaluates attention, visual scanning, the speed of eye-hand coordination, and information processing. Part B assesses working memory and executive functions associated with the capacity to switch between sets of stimuli. The resulting scores include difference (B-A), ratio (B/A), and proportion (B-A/A).
Stroop color word task (Golden, 1978)	Selective attention, inhibitory control, and cognitive flexibility	The Stroop Test evaluates cognitive flexibility and attention span through a series of three distinct subtests. In each subtest, there are 100 items organized in 5 columns with 20 items per column. The time allocated for each subtest is limited to 45 seconds. In the initial subtest, individuals are instructed to verbally read aloud the color names (such as red, green, or blue) that are written in black ink. For the second subtest, participants are presented with three letters “X” printed in red, green, or blue and are required to state the color of the ink. In the third subtest, subjects are asked to announce the color of the ink in which the words are printed (for instance, if the word “blue” is printed in green ink, the individual should say “green”). The time taken to complete each task and the number of errors made are recorded. The total score is calculated as the sum of scores from all three subtests, or alternatively, an interference index can be determined by subtracting the time taken to complete the color-naming trial from the word-reading trial.
Letter-number sequencing from WAIS-III (Wechsler, 2008)	Working memory	In the Letter-Number Sequencing task, individuals are presented with a series containing a mix of letters and numbers. Their task involves repeating these sequences by initially stating the numbers in ascending order and subsequently reciting the letters in alphabetical order. The score is determined by the count of correctly manipulated lists.

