**Qualitative outcome**		
Semi-structured interview	Subjective effects and feasibility	Semi-structured interview asking about motivation, expectations, the need of any adjustment in the program, the difficulties that participants struggled during the program (e.g., time restriction, physical limitation, anxiety, financial problems), if participants realized any change in their daily life due to the program and so were motivated to keep practicing during and after the program, if the group was supportive for the development of the program, if participants keep using the techniques learned at the follow-up session, perceived effects, and suggestions.

*GAI* Geriatric Anxiety Inventory, *GDS-5* Geriatric Depression 5 Item Scale, *HRV* Heart rate variability, *MAAS* The Mindfulness Attention and Awareness Scale, *MMSE* The Mini Mental State Examination, *PPS* Perceived Stress Scale, *PSQI* Pittsburgh sleep quality index, *TMT* Trail making test

Previous reviews have shown that mindfulness may improve executive attention (mental set shifting and inhibition), as well as working memory, but overall evidence remains limited [32, 56, 68]. One study has shown the recruitment of attentional control regions such as the prefrontal cortex and anterior cingulate cortex in participants during meditation activities [69]. Additionally, older adults have shown to benefit of mindfulness in cognition, especially on attention regulation [70, 71]. Therefore, primary outcomes will be the executive functioning measures, namely the score on TMT, Stroop color word task, and letter-number sequencing from WAIS-III [72].

We will run exploratory secondary analyses including the following measures: the Pittsburgh sleep quality index (PSQI), Perceived Stress Scale (PPS), Mindfulness Attention and Awareness Scale (MAAS), Geriatric Anxiety Inventory (GAI), Geriatric Depression 5 Item Scale (GDS-5), the Mini Mental State Examination (MMSE) scores, as well as cortisol levels and heart rate variability (HRV). Cortisol level was only assessed at baseline and during post-intervention assessment (not in follow-up session, as the financial resources are limited). For the self-reported measures, the total score for the scale and subscales will be used as outcomes.

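### One of the two scores offered for the primary Stroop outcome takes a difference of completion times in a test capped at 45 seconds and, read naturally, leaves out the conflict subtest

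*Protocol article*

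**What the plan says.** The text following Table 4 (Outcome measures) states that the "primary outcomes will be the executive functioning measures, namely the score on TMT, Stroop color word task, and letter-number sequencing from WAIS-III". Table 4 gives the construct of the Stroop as "Selective attention, inhibitory control, and cognitive flexibility".

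The same table row describes the test. "In each subtest, there are 100 items organized in 5 columns with 20 items per column", and "The time allocated for each subtest is limited to 45 seconds". The three subtests are:

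- Subtest 1, words printed in black: "In the initial subtest, individuals are instructed to verbally read aloud the color names".
- Subtest 2, strings of the letter X: these are "printed in red, green, or blue and are required to state the color of the ink".
- Subtest 3, colour words printed in a conflicting ink: the participant names the ink.

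The row then says that completion time and number of errors are recorded. It does not mention a count of items done within the limit. Two scores follow. The first is described thus: "The total score is calculated as the sum of scores from all three subtests". The second is introduced as an alternative: "an interference index can be determined by subtracting the time taken to complete the color-naming trial from the word-reading trial". Neither is named as the one to be analysed.

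**The concern.** Two parts of one table row do not fit together. A test stopped at a fixed limit yields a number of items completed. A difference of completion times suits a test in which everyone works to the end of the card. Under a cap, time carries information only for participants fast enough to finish early.

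The index is also called an interference index, but it appears to be built from the two subtests without interference. Subtest 3 is the only one in which word and ink compete, and it is not named in the definition.

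At stake is whether this measure can speak to the main hypothesis, stated in the Discussion, that the MBSR arm will gain more in executive functioning. If the index were the score analysed, a real change in inhibition could leave it unmoved. Leaving the choice of score open adds a second risk: under Randomization and blindness, the article says that the data analyst is not blinded to allocation.

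**Working it through.** The plan gives no Stroop values, so there is no figure to reproduce. The check applies the stated rule to the stated test.

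**Inputs from Table 4.** Items per subtest: 100. Limit: 45 s. Index: word-reading time minus colour-naming time.

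**Step 1, the pace needed to finish.** 100/45 = 2.22 items per second, that is 45/100 = 0.45 s per item. Anyone slower has a recorded time of 45 s.

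**Step 2, the recorded time.** If a participant would complete n items in 45 s at a steady pace, the time is min(45, 45 × 100/n). If n is below 100 on both cards, the index is 45 − 45 = 0.

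**Step 3, illustration.** The profiles below are assumptions, chosen to span slow to fast. W, C and CW are the items that would be done in 45 s on subtests 1, 2 and 3.

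| W / C / CW | Index, colour naming = subtest 2 | Index, colour naming = subtest 3 | Total W + C + CW | CW − WC/(W + C) |
|---|---|---|---|---|
| 60 / 45 / 20 | 45 − 45 = 0 | 45 − 45 = 0 | 125 | −5.7 |
| 80 / 60 / 30 | 0 | 0 | 170 | −4.3 |
| 95 / 70 / 40 | 0 | 0 | 205 | −0.3 |
| 110 / 80 / 45 | 40.9 − 45 = −4.1 | 40.9 − 45 = −4.1 | 235 | −1.3 |
| 120 / 105 / 60 | 37.5 − 42.9 = −5.4 | 37.5 − 45 = −7.5 | 285 | 4.0 |

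For simplicity, the total and the last column treat W, C and CW as the counts scored, although a 100-item card stops counting at 100. The last column is one example of a count-based interference score; it does not come from the documents.

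**Step 4, what the table shows.**

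- In the first three profiles the colour-word result doubles from 20 to 40, yet the index is 0 each time under either reading.
- In the fourth profile only the word card is finished. The value of −4.1 s would be the same for any colour-naming pace at or below 100 items, so it reflects reading speed alone.
- In the last two profiles, with colour naming taken as subtest 2, the index does not depend on CW at all.
- With colour naming taken as subtest 3, the conflict subtest enters in principle. In all five profiles it sits at the 45 s cap, so it contributes a constant.
- The total moves with CW one for one when W and C are unchanged, and moves equally with plain reading or naming speed.

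**Step 5, what the summed scores are.** The row does not say whether they are counts or times. If they were times, anyone who finished no card would have a total of 3 × 45 = 135 s.

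**The case against.** The best defence is that Table 4 describes an instrument and does not commit the trial to the index. The index is worded as an option, the text elsewhere refers only to the Stroop score, and the final choice may sit in an analysis plan that is not shown. A journal article condenses. This stands in part: the index may never be used, and silence about the chosen score would not be an error in itself. But condensing explains an omission. It does not explain a stated scoring rule that conflicts with the time limit given in the same table row.

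Second, the article attaches the name colour-naming trial to no particular subtest, and subtests 2 and 3 both ask for the ink colour. Subtest 2 is the more natural reading, but subtest 3 is possible. The omission of the conflict subtest therefore depends on that reading; the cap problem does not.

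Third, a reader might infer more than the documents support:

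- *That the Stroop outcome is constant for most participants.* No Stroop values are given, the limit is an upper bound so fast participants can finish early, and two of the five assumed profiles give non-zero values. An older population with little schooling makes capped times plausible but does not give their share.
- *That neither score can show an effect on executive control.* The total contains the colour-word subtest and, if built from counts, registers a gain in it, diluted by the other two.
- *That the total is mostly processing speed and must be demoted.* No figure supports this. The listed construct is broad, and a less specific score is a choice, not a misstatement.

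**Conclusion.** The time-difference index is wrong as written. Given the 45 s limit, it equals 0 for every participant slower than 2.22 items per second on both cards, at every visit where that holds. This follows from the protocol's own figures and needs no assumption beyond recording 45 s for an unfinished card. How many participants it affects cannot be determined from the documents.

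On the natural reading of the subtest descriptions, the index also contains no conflict condition, so it cannot reflect inhibitory control even in fast participants.

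The fault is confined to one of two offered scores for one of three primary measures. The Trail Making Test and letter-number sequencing are untouched, and the three-subtest total remains usable as a general score, though it does not isolate interference. The open choice between two different scores matters more here because the analyst knows the allocation.

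**What to change.** Delete the time-difference index. Name one primary Stroop score before any outcome data are examined by arm. Base it on items correct in 45 s, include the colour-word subtest, and say whether higher is better. One example is the colour-word count adjusted for the word and colour counts at the same visit, such as CW − WC/(W + C), where higher means less interference. The three-subtest total may be kept if it is labelled a general score and its units are stated.

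The cost is a change of scoring wording, provided the counts exist. The sponsor must check this first: Table 4 lists only times and errors as recorded, and Study setting says that data are already being collected. The check should confirm that items completed or correct are on the forms at baseline, post-intervention and follow-up. If they are not, recording should start at once and the article should say which visits lack them, since a count not written down may not be recoverable. The planned sample size of 90 rests on an assumed standardised effect (f = 0.14), not on a particular Stroop score, so its calculation does not need to change.

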***Secondary outcomes***		
PSQI (del Rio João et al., 2017)	Sleep quality	The PSQI is a questionnaire comprising 19 items designed to assess sleep quality and disruptions over a one-month period. There are five supplementary questions that require responses from the participant’s roommate. These questions are divided into seven distinct categories: 1) subjective sleep quality, 2) sleep latency, 3) sleep duration, 4) usual sleep efficiency, 5) sleep disturbances, 6) use of sleeping medication, and 7) daytime dysfunction. The cumulative scores from these categories yield a global score ranging from 0 to 21, with a higher score indicating poorer sleep quality. An overall PSQI score exceeding 5 suggests significant difficulties in at least two of these categories or moderate difficulties in more than three of them.
PPS (Mota-Cardoso et al., 2002)	Perceived stress	The PSS is a five-point Likert scale consisting, designed to evaluate the individual’s perception of stress. In its Portuguese version, it comprises 10 items. Participants are asked to assess the frequency of their emotions and thoughts concerning situations that have arisen in the past month. Responses range from “never” to “very often.” Four of the items are positively worded and are subsequently reverse scored before being combined with the negatively worded items. The resulting score falls within a range of 0 to 40, with a higher score indicating a heightened level of stress perception.
MAAS (Gregório & Pinto-Gouveia, 2013)	Dispositional quality of mindfulness	The MAAS evaluates the dispositional aspect of mindfulness, particularly focusing on the attention and awareness that individuals have in their daily life experiences. This assessment comprises 15 items, and the overall score is derived by summing the individual scores. The scoring scale ranges from 15 to 90, with higher scores indicating a higher degree of mindfulness.
GAI (Ribeiro et al., 2011)	Anxiety symptoms	The GAI is a tool designed to evaluate anxiety symptoms in older individuals. It comprises a set of 20 statements where respondents indicate their agreement or disagreement. The recommended threshold for identifying severe anxiety symptoms is when the score reaches 8 or 9.
GDS-5 (Santos et al., 2019)	Depressive symptomatology	The GDS-5 represents a condensed version of the Geriatric Depression Scale, consisting of only five items. It serves as a screening tool for detecting depressive symptoms among older individuals. In the Portuguese adaptation, there are only four items and they are scored with either 0 or 1. The overall score is derived by summing these items, and the suggested cutoff point for identifying depressive symptoms is set at 2 points.
MMSE (Freitas et al., 2015)	General cognitive state	The MMSE is a brief screening assessment that offers a concise evaluation of cognitive abilities. It encompasses various tasks to assess orientation regarding time and place, the ability to register information, attention and calculation skills, spontaneous recall, language proficiency (including naming, repetition, reading, and spontaneous writing), and visual construction aptitude. Participants receive one point for each correct response, with a maximum achievable score of 30 points upon completion.
Salivary Cortisol	Stress marker	Saliva samples are gathered for cortisol analysis through the utilization of Salivette assays. These samples are obtained immediately upon waking, as well as at 30 minutes and eight hours after awakening. Various indices related to diurnal cortisol measurements, such as the peak cortisol level and the area under the curve concerning the baseline, will be thoroughly examined (Fekedulegn et al., 2007; Lenze et al., 2012).
Resting heart rate variability - HRV (Kim et al., 2018)	Surrogate for psychological health and stress	HRV pertains to the fluctuations in the duration of intervals between heartbeats. It is closely linked to the heart’s capacity to respond to a range of physiological and environmental stimuli. Reduced HRV is associated with compromised regulation and homeostatic functions of the autonomic nervous system, which in turn diminishes the body’s ability to handle stressors effectively. One of the simplest time-domain analysis metrics is the standard deviation of the NN interval (SDNN). A higher SDNN value indicates a greater level of HRV. Another commonly utilized index is the root mean square of the successive differences (RMSSD), which is essentially the square root of the mean of the sum of the squares of differences between adjacent NN intervals.
***Screening***		
Sociodemographic and health-related information	Sociodemographic and health-related information	It is a structured interview in which participants answered questions regarding age, gender, years of formal education, country of origin, number of years living in Luxembourg, mother language, marital status, professional occupation, people living in the household, disease history, surgical interventions, pharmacological treatments, health complaints, difficulties in daily life, psychological intervention, mindfulness or meditative practices, religion, physical exercise, weight, and height.
DSM-5 Self-Rated Level 1 Cross-Cutting Symptom (Bastiaens & Galus, 2018)	Assessment of psychopathology	The DSM-5 is a screening tool to assess various forms of psychopathology, including depression, anger, mania, anxiety, somatic symptoms, suicidal ideation, psychosis, sleep disturbances, memory issues, repetitive thoughts and behaviors, dissociation, personality functioning, and substance use. For this specific protocol, we have chosen to focus solely on items related to the domains of mania, suicidal ideation, psychosis, and substance use. Each item is evaluated using a 5-point scale, where 0 represents the absence of symptoms or no occurrence, 1 indicates mild or infrequent symptoms occurring for less than 2 days, 2 denotes mild symptoms experienced over several days, 3 signifies moderate symptoms occurring on more than half of the days, and 4 indicates severe symptoms experienced nearly every day. A rating of 2 or higher is considered a potential indicator for further investigation. However, for substance use and suicidal ideation, a rating of 1 is used as the cutoff point for considering additional inquiry.
**Qualitative outcome**		
Semi-structured interview	Subjective effects and feasibility	Semi-structured interview asking about motivation, expectations, the need of any adjustment in the program, the difficulties that participants struggled during the program (e.g., time restriction, physical limitation, anxiety, financial problems), if participants realized any change in their daily life due to the program and so were motivated to keep practicing during and after the program, if the group was supportive for the development of the program, if participants keep using the techniques learned at the follow-up session, perceived effects, and suggestions.

*GAI* Geriatric Anxiety Inventory, *GDS-5* Geriatric Depression 5 Item Scale, *HRV* Heart rate variability, *MAAS* The Mindfulness Attention and Awareness Scale, *MMSE* The Mini Mental State Examination, *PPS* Perceived Stress Scale, *PSQI* Pittsburgh sleep quality index, *TMT* Trail making test

Previous reviews have shown that mindfulness may improve executive attention (mental set shifting and inhibition), as well as working memory, but overall evidence remains limited [32, 56, 68]. One study has shown the recruitment of attentional control regions such as the prefrontal cortex and anterior cingulate cortex in participants during meditation activities [69]. Additionally, older adults have shown to benefit of mindfulness in cognition, especially on attention regulation [70, 71]. Therefore, primary outcomes will be the executive functioning measures, namely the score on TMT, Stroop color word task, and letter-number sequencing from WAIS-III [72].

We will run exploratory secondary analyses including the following measures: the Pittsburgh sleep quality index (PSQI), Perceived Stress Scale (PPS), Mindfulness Attention and Awareness Scale (MAAS), Geriatric Anxiety Inventory (GAI), Geriatric Depression 5 Item Scale (GDS-5), the Mini Mental State Examination (MMSE) scores, as well as cortisol levels and heart rate variability (HRV). Cortisol level was only assessed at baseline and during post-intervention assessment (not in follow-up session, as the financial resources are limited). For the self-reported measures, the total score for the scale and subscales will be used as outcomes.

A cortisol test measuring the diurnal cortisol cycle is done with saliva samples collected at the participants’ home following manufacturer’s instructions (Salivette®, Sarstedt, Nümbrecht, Germany). Saliva collection is self-administered before and upon completion of the intervention, at three time points: 1) upon waking up, 2) 30 minutes after waking up, and 3) at 8 hours after waking up. Sarstedt salivette® kits are delivered to participants at baseline and after the intervention. Participants receive explanations on how to collect the saliva, specifically, participants are told to remove the swab from the Salivette® and place it in the mouth for about 120 seconds. Then, they return the swab to the Salivette®, replace the stopper, and store the sample in the home fridge. Normally, up to 1 day after saliva collection, participants themselves bring the collected samples to the place of intervention and give them to [name] who brings the samples to the laboratory for processing, analysis, and storage. At the laboratory, salivettes are stored frozen for up to 7 days (the tests are done once a week). Samples are centrifuged at 1000 rpm and aliquots are analysed by ELISA (Demeditec Saliva Free Cortisol Kit – Demeditec DES6611, Demeditec Diagnostics GmbH, Kiel, Germany) following the user manual. The samples are diluted if the results are greater than 30 ng/ml.

Heart rate (HR) assessments are performed individually during rest at baseline, post-test, and follow-up sessions. Participants comfortably sit using a Polar H10 chest strap and are instructed to lean back in the chair, to relax, and avoid movement for 15 minutes. In the last 5 minutes, HR is recorded using the Elite HRV smartphone application (Elite HRV Inc., Asheville, NC, USA). Each HR measure is recorded at two different times on the same day.

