### Randomization and blindness

At the end of the baseline assessment, participants are randomized to the MBSR or the health promotion program intervention. The randomization list was generated through a website (http://www.randomization.com) in blocks of 10 participants with a ratio of 1:1 to receive the MBSR or the health promotion program (i.e., five individuals randomly allocated to each group). The allocation list is masked from all study personnel. The condition of each participant is described in different excel sheets in a way that the researcher responsible for the randomization would only have access to the allocation of the next participant (allocation concealment). Assessors and participants are blinded to the conditions prior to randomization. During the intervention, although participants know which activity they are included in, they do not know which the experimental or control conditions are. If participants want to know about our hypotheses, they may be disclosed after the study is completed. To test participants’ blinding, they fill out a questionnaire of credibility and expectancy adapted from Devilly and Borkovec [73]. Due to the researchers’ availability, the intervention facilitator and the data analyst are not blinded for participants’ conditions since it is performed by the first author of this study ([name]).

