### Statistical analyses

Regarding statistical analyses, data will be explored for missing and impossible values and descriptive statistics will be provided. The analyzes will be based on the modified intention-to-treat (mITT) population (i.e., participants that participated in at least three group-sessions and have at least one post-intervention assessment). We chose three sessions based on previous studies showing cognitive changes after three sessions of cognitive training [74]. A level of significance of less than 5% will be used in the analyses.

We will use mixed-effect regression models with maximum likelihood estimation to analyze change in cognitive scores as a function of the interaction group*time and participants will be treated as a random effect. *P*-value will be set at *p* < .05. Effect sizes (Hedges, *g*) will be calculated for each score [75–77]. Demographic factors, such as gender and educational level, the number of attended sessions, as well as the score differences in stress relief, depression, anxiety, mindfulness state, and sleep quality will be analyzed by running separate models for each factor.

Concerning the interview, it will be recorded in audio and transcribed in Portuguese by a member of the research team. The interview data will be analyzed according to Malterud’s principles of systematic text condensation and guidelines for qualitative research [78]. Content analysis can be conducted using the software package NVivo 12 [79].

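### Three co-equal primary tests, with the TMT and Stroop scores left open and an unadjusted 5% level: if any one significant test counts as success, the false-positive chance is about 10% to 14%

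*Protocol article*

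**What the plan says.** Under Outcome measures, the text after Table 4 states that "primary outcomes will be the executive functioning measures, namely the score on TMT, Stroop color word task, and letter-number sequencing from WAIS-III". The three tests stand side by side, with no order and no composite.

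Table 4 describes the scoring of each test:

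- **TMT:** "The resulting scores include difference (B-A), ratio (B/A), and proportion (B-A/A" – three derived scores, none singled out.
- **Stroop:** "The total score is calculated as the sum of scores from all three subtests, or alternatively, an interference index can be determined" – one score or another. The index is described as a difference between colour-naming and word-reading times, while each subtest is limited to 45 seconds.
- **Letter-number sequencing:** "The score is determined by the count of correctly manipulated lists" – one score.

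Under Statistical analyses: "A level of significance of less than 5% will be used in the analyses". Change in cognitive scores is analysed through the group-by-time interaction in a mixed model, and effect sizes "will be calculated for each score".

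Under Sample size estimation, 90 participants (45 per arm) are derived for one group-by-time interaction with f = 0.14, 80% power, 5% type I error and 5% attrition.

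Under Randomization and blindness, the article discloses that "the intervention facilitator and the data analyst are not blinded", because the first author fills both roles.

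**The concern.** The trial is described as a superiority trial, and its main hypothesis is a larger gain in executive functioning under MBSR. Three tests can each speak to that hypothesis at 5%, and nothing says how their results combine into one conclusion. A report could rest the claim on whichever test reached significance. The sample size treats the question as a single test, so the design and the analysis do not describe the same decision.

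Two of the three tests also lack a fixed score. That leaves a choice to be made later, by an analyst who knows the allocation.

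**Working it through.** **Inputs from the article.** Three primary tests; 3 TMT + 2 Stroop + 1 letter-number scores listed; 0.05 level without division; f = 0.14; 80% power; 5% attrition; N = 90; assessments at T1, T2 and T3.

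**Assumed, because the article does not give them.** Within-person correlation rho; sphericity; correlation r between the test statistics of different scores.

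**1. The stated sample size.** For the repeated-measures ANOVA interaction with two groups and m time points, lambda = f² × N × m / (1 − rho), with df1 = m − 1 and df2 = (N − 2)(m − 1). With m = 3, rho = 0.5 and N = 84, lambda = 0.0196 × 84 × 3 / 0.5 = 9.88 on 2 and 164 df, which gives 80% power. Then 84 / 0.95 = 88.4, so 89, or 90 for equal arms. The stated figure is reproduced, for one test at 5%. (With m = 2, the same N needs rho of about 0.6; rho = 0.5 would need 110 randomised.)

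**2. Counting the scores.** The TMT proportion is read as (B − A)/A, since the inner brackets are missing in Table 4. Then (B − A)/A = B/A − 1. Subtracting a constant changes neither the interaction estimate nor its standard error, so ratio and proportion always give the same p-value. Of the six listed scores, at most five are distinct.

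**3. Chance of at least one false positive if any one result counts.** For k independent tests this is 1 − 0.95^k: for k = 3, 1 − 0.857 = 14.3%; for k = 5, 1 − 0.774 = 22.6%. With correlation, equally correlated two-sided normal statistics were simulated, which approximates the interaction tests.

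| Tests at 0.05 each | independent | r = 0.5 | r = 0.8 |
|---|---|---|---|
| 3 (one score per test) | 14.3% | 12.5% | 9.8% |
| 5 (all distinct scores) | 22.6% | 18.4% | 12.7% |

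**4. If all three tests had to be significant.** The chance of a false claim is then at most 5%. Power cannot exceed that of a single test. With 90 × 0.95 = 85.5, about 86 evaluable, single-test power is 81% at rho = 0.5. If the three tests were independent and each had the planning effect, joint power would be 0.813³ = 54%. Correlation between the tests raises this, with 81% as the ceiling. The sample size makes no allowance for this rule.

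**5. Power of one given test at Holm's first step** (N = 86, f = 0.14, m = 3):

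| rho (assumed) | at 0.05 | at 0.05/3 |
|---|---|---|
| 0.3 | 66% | 49% |
| 0.5 | 81% | 67% |
| 0.7 | 96% | 91% |

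**The case against.** The strongest reply is that a separate analysis plan, not shown, may hold a multiplicity rule, and that a condensed article need not repeat it. That would answer a complaint about silence alone. Here the article itself names several primaries, lists alternative scores and sets an unadjusted level, so the point is fixed badly and not merely left out.

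Four stronger readings are tempting, and the article does not support them:

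- **That 5% is certainly exceeded.** This holds only if any one significant result counts as success. The article does not say so, and a rule requiring all three tests would hold 5%.
- **That six scores are planned as six tests.** Table 4 gives the scores in a description column, the text speaks of the TMT score in the singular, and the Stroop wording offers one score or the other. This is an unmade choice. The five-score row shows what would follow if every distinct score were tested.
- **That T2 and T3 double the number of tests.** The analysis and the sample size both use one group-by-time interaction. No separate tests at each visit are stated.
- **That the unblinded analyst raises the error rate.** The arrangement is disclosed with its reason and does not itself change alpha. It matters only because the scores are still open to choice.

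It also stands that the correlations are assumptions. Even so, three tests at r = 0.8 give about twice 5%.

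**Conclusion.** The concern holds in a conditional form. The article has three co-equal primary tests, two of them without a fixed score, an unadjusted 5% level, and a sample size for a single test. If one significant test suffices, the chance of a false claim is about two to three times the nominal level: 14% with independent tests, falling to 10% at an assumed correlation of 0.8. If all three are required, the level is held, but power is generally below the single-test figure on which N = 90 rests. Neither rule is stated, so the primary claim has no defined test.

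The duplicate TMT score follows from algebra, given the natural reading of the proportion. The unblinded analyst adds a risk of selective score choice, which fixing the scores in advance would remove.

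**What to change.** Before any unblinded analysis:

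1. **Fix one score per test.** For TMT, drop the proportion as a duplicate of the ratio and choose between difference and ratio. For Stroop, choose a score that uses the incongruent (third) subtest and fits the 45-second limit. The index in Table 4 does neither: it compares only colour naming and word reading, and it uses completion times although each subtest is time-limited. Letter-number sequencing keeps its count.
2. **State the success rule.** Either name one of the three as the single primary, or a fixed test order, at 5%; or keep all three and apply Holm. A composite tested once at 5% is a further option, but only if all scores are first aligned so that higher means better. Larger TMT scores are worse and larger letter-number counts are better, so a plain mean of standardised scores would let benefits cancel.
3. **Report every other score as exploratory.**

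The cost is wording and a registry update, which the article already foresees for protocol changes. A single named primary or a composite costs no alpha, and a fixed order costs none for its first test. With Holm, the first-step power for a given test is about 67% instead of 81% at rho = 0.5 (49% versus 66% at 0.3; 91% versus 96% at 0.7). Later Holm steps use larger levels, so this is not the full cost of the procedure.
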